### Data collection and outcome measures

Baseline questionnaires will be administered at the initial consultation by the treating practitioner. Baseline data will include demographic and clinical characteristics including participant gender, age, work status, functional impairment, treatment history and medical history, pain rating, self-efficacy, catastrophizing, stress anxiety and depression scores and work ability. Outcome data will be collected through questionnaires at 8-, 26- and 52 weeks follow-up. In addition, a verbal pain measure will be taken by the treating practitioner at time of treatments on an 11-point VAS.

#### Primary outcomes

The primary outcomes are between group differences in self-efficacy, measured using the Pain Self Efficacy Questionnaire (PSEQ) and disability measured using the Roland Morris Disability Questionnaire (RMDQ) at the conclusion of treatment (8 weeks), 6- and 12-month follow up. The PSEQ is a 10-item questionnaire that measures self-efficacy on a scale from 0 to 60, where a higher score reflects higher self-efficacy [32]. A higher self-efficacy rating correlates with a patient’s strong belief that they can manage to execute an activity. This scale has strong psychometric qualities [33] with alpha values reported as 0.93 [32]. The RMDQ is a 24 item questionnaire that scores an individual’s level of disability from 0 to 24, ranging from no disability (0) to severe disability (24) [34]. The responsiveness rate of the RMDQ has been calculated to be between 0.76–0.78 in some studies [35].

#### Secondary outcomes

Secondary outcomes include Pain Catastrophizing Scale (PCS) [36], Patient Specific Functional Scale (PSFS) [37], Depression Anxiety and Stress Scale (DASS21) [38], Pain Numerical Rating Scale (PNRS) [39] and Work Ability, using the single item Work Ability Index (WAI) score [40] at baseline, 8 weeks, 6 months and 12 months.Pain Catastrophizing Scale (PCS) measures a person’s tendency to excessively focus on the sensations of pain (rumination), the threat of pain (magnification), and to subordinate to a feeling that they have no control over the intensity of pain (helplessness) [41]. Three subscale scores describe the levels of rumination, magnification and helplessness. This scale has high internal reliability [42] (coefficient alphas: total PCS = 0.87, rumination = 0.87, magnification = 0.66, and helplessness = 0.78 [36].Using the Patient Specific Functional Scale (PSFS) participants are asked to identify three important activities that they are unable to do, or have difficulty doing because of their LBP. Each is scored between 0 and 10 on a Likert scale. The PSFS tool is used to quantify any activity limitations, as well as measuring any functional improvements or outcomes over time [37].The DASS21 is a validated 21 question tool that measures depression, anxiety and stress in adults [38]. It has been developed as a short form of the DASS, which is a self-reported scale with three subscales; Depression (DASS-D), Anxiety (DASS-A) and Stress (DASS-S). The psychometric properties of this scale have been noted as 0.94 (DASS-D), 0.87 (DASS-A) and 0.91 (DASS-S) [43].The Pain Numeric Rating Scale measures a participant’s pain intensity on an 11 point scale (0-10). Participants are asked about their present pain, as well as pain intensity over the preceding week for: usual, best and worst pain levels. The scale is a valid and sensitive tool [39].This trial uses a modified version of the full 7 sectioned WAI that has been assessed for validity and reliability by the European Network for Workplace Health Promotion (ENWHP) and National WAI Network [40]. The question is: “Rate your work ability now, compared to your life time best, on a scale of 1 to 10 (1 is worst, 10 is best)”. A higher score indicates the person’s good self-reported work ability, and conversely, a lower value indicates indicated a jeopardised work ability rating.

#### Statistical methods

The primary data analyses will be conducted using linear mixed models to test for between group differences in post-treatment PSEQ and RMDQ. A covariance structure will be selected that provides the best fit and then will be included as a random factor to adjust for a possible cluster effect of site. A group by time interaction will be included to allow least significant difference (LSD) contrasts to be obtained between groups at each time point. Because linear mixed models allow for missing data points, no imputation of missing data values will be required. Analysis will be by intention-to-treat with the statistician blinded to patient group allocation.

In secondary analyses, analysis of covariance will be used to test whether regression to the mean has occurred, that is whether the patient’s response is related to baseline values. In this, separate analyses will be conducted to determine the effects of treatment at −8, −26 and −52 weeks.

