#### Sample size calculations

With an estimated moderate post-treatment between-group effect size (Glass’s delta) of 0.60 SD, a sample size of 46 per group would be required to show statistical significance (power of 80 %, alpha = 0.05) using a LSD post hoc test in a linear mixed model (equivalent to an independent samples *t*-test). Allowing for a 15 % dropout, 108 participants in total will be recruited. We are assuming that the potential loss of power as a result of a cluster effect will be balanced by the use of linear mixed models to negate the effects of missing values and the increased power gained by adjusting for between visit correlations.

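### The primary mixed model, as described, does not adjust for baseline PSEQ or RMDQ; it is valid but gives up precision that the trial could have at no cost

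*Protocol article*

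**What the plan says.** All references are to the protocol article.

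- **Statistical methods, primary analysis:** "The primary data analyses will be conducted using linear mixed models to test for between group differences in post-treatment PSEQ and RMDQ". The contrast is then defined: "A group by time interaction will be included to allow least significant difference (LSD) contrasts to be obtained between groups at each time point". Site enters as a random factor. No baseline covariate is named, and nothing says that the groups share a baseline mean.
- **Statistical methods, secondary analysis:** "In secondary analyses, analysis of covariance will be used to test whether regression to the mean has occurred". The section goes on to say that "separate analyses will be conducted to determine the effects of treatment at" 8, 26 and 52 weeks.
- **Sample size calculations:** 46 per group for 0.60 SD, 80% power and alpha 0.05, "using a LSD post hoc test in a linear mixed model", which the section equates with a two-sample t-test. A 15% dropout allowance gives 108. No participants are added for clustering. Its cost is assumed to be offset by the mixed model's handling of missing values and by extra power from the correlation between visits.
- **Data collection and outcome measures:** "Baseline questionnaires will be administered at the initial consultation by the treating practitioner". The baseline list includes "functional impairment, treatment history and medical history, pain rating, self-efficacy". Under Randomisation and blinding, allocation follows that consultation, so these scores precede randomisation.

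**The concern.** Both primary outcomes are questionnaire scores measured repeatedly on the same people, and a person's baseline score usually predicts the later one. A comparison that ignores it leaves that predictable variation in the error term, and the confidence interval is wider than it need be. Any chance difference between the groups at baseline also passes in part into the estimate.

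Two consequences are specific to this plan. First, treatment effects at the same three visits will come from two analyses, and the less precise one is primary. If they differ, switching to the adjusted result after the data are seen would look selective. Second, the sample size argument relies on a gain from between-visit correlation that the described contrast may not provide.

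**Working it through.** **Inputs.** From Sample size calculations: effect 0.60 SD, alpha 0.05 (taken as two-sided, which fits the stated figure), power 80%, 46 analysed per group, 15% dropout, 108 in total. The correlation r between baseline and follow-up is not given; 0.3 to 0.7 is assumed.

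**1. The plan's own figure.** A two-sample t-test at 0.60 SD needs 45 per group for 80% power (44 by the normal approximation). At 46 per group the t-test has power 0.812. For dropout, 92 / 0.85 = 108.2, against the stated 108. The sample size therefore reproduces from an unadjusted comparison. A one-sided test would need 35, which does not fit.

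**2. Gain from baseline adjustment.** Adjustment multiplies the variance of the contrast by 1 − r². Power is then that of a t-test at 0.60 / √(1 − r²) with 46 per group. The equivalent unadjusted size is 46 / (1 − r²), and the effect detectable with the same power is 0.60 × √(1 − r²).

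| r (assumed) | variance factor | power at 46 per group | equivalent unadjusted n per group | effect detectable with the same power |
|---|---|---|---|---|
| 0 (as planned) | 1.00 | 0.81 | 46 | 0.60 SD |
| 0.3 | 0.91 | 0.85 | 51 | 0.57 SD |
| 0.5 | 0.75 | 0.91 | 61 | 0.52 SD |
| 0.7 | 0.51 | 0.98 | 90 | 0.43 SD |

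**3. Does it matter whether baseline is one of the time levels?** The article does not say. The generalised least squares variance was computed for four visits with equal correlation, 46 per group and complete data. Whether the model uses follow-up visits only or adds baseline with a free mean in each group, the standard error of a single-visit contrast is √(2/46) = 0.209 SD at every r. That equals the t-test. With one common baseline mean it is 0.209 × √(1 − r²) = 0.199, 0.181 and 0.149 SD. The gain comes from the covariate or the common mean, not from including baseline as a visit.

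**4. The between-visit correlation argument.** By step 3, the described contrast gains nothing from the correlation when data are complete. With missing visits it recovers part of what was lost. Take 54 recruited per group and each follow-up visit missing at random with probability 0.15. A single-visit t-test then has 54 × 0.85 = 45.9 per group. Averaging the information over the missing-visit patterns gives these effective numbers per group:

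| r (assumed) | free baseline means | common baseline mean |
|---|---|---|
| 0.3 | 47.0 | 51.0 |
| 0.5 | 48.5 | 62.6 |
| 0.7 | 50.4 | 93.0 |

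The small rise in the middle column is the missing-value benefit, which the sample size section already counts as its other offset. It cannot exceed 54.

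**5. Chance imbalance.** With 46 per group the baseline difference has SD √(2/46) = 0.209 SD, so it exceeds 0.2 SD in either direction about 34% of the time. Given such a difference, the unadjusted estimate moves by about r × 0.2, which is 0.1 SD at r = 0.5, or one sixth of 0.60. Simulation (800 trials per setting, complete data) gave slopes on the imbalance of 0.30, 0.53 and 0.69 for the unadjusted contrast at r = 0.3, 0.5 and 0.7, and about 0 for the common-mean model.

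**The case against.** **The article is silent rather than decided.** It gives no full list of fixed effects, and covariates are often left to an analysis plan, which may exist. The t-test remark stands in the sample size section, where sizing on an unadjusted test is a common conservative choice. This has some force, and it is why the point is limited to the model as described. But the article does more than stay silent: it defines the primary contrast, names site as the adjustment, and places analysis of covariance among the secondary analyses.

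**Adjusted effects will be reported anyway.** On the natural reading, the secondary analyses give baseline-adjusted treatment effects at each follow-up. That stands. What remains is which result is primary.

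**Nothing is invalid.** This also stands. A reader might infer that the primary result is biased, or that the trial is underpowered for this reason. The documents support neither: the unadjusted estimate is unbiased over randomisations, and 46 per group gives 81% power against a target of 80%. Nor is chance imbalance a further loss on top of lost precision, because the unadjusted standard error already includes it.

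**The gain rests on an assumed correlation.** True. At r = 0.3 power rises only from 81% to 85%, and the correlation could be lower at 52 weeks than at 8.

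**Baseline RMDQ is not named.** The baseline list names self-efficacy, but disability appears only as functional impairment. It is reasonable to take this as the RMDQ, since the planned analysis of covariance needs a baseline value, but the article does not say so.

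**Conclusion.** The point holds as a worthwhile improvement, not as an error that must be corrected. As described, the primary contrast is not adjusted for baseline PSEQ or RMDQ. It is valid and adequately powered on the plan's own terms. It forgoes a reduction in variance of 9%, 25% or 49% at assumed correlations of 0.3, 0.5 or 0.7. Having baseline as a time level would not recover this unless the groups share a baseline mean.

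The sample size section's appeal to between-visit correlation is not borne out by this contrast beyond partial recovery of missing visits. That does not show that clustering leaves the trial short of power, because the article gives no figure for the cluster effect.

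The calculations assume equal variances, equal correlation across visits and visits missing at random. The choice of covariance structure is a separate matter and is not part of this point.

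**What to change.** Before unblinding, specify the primary model for each outcome in one of two ways:

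- follow-up scores at 8, 26 and 52 weeks on group, visit, group-by-visit, baseline score of that outcome and baseline-by-visit, with site as planned; or
- baseline and follow-up scores together as outcomes, with the baseline mean constrained to be the same in both groups.

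Report the resulting group contrast at each visit as primary. The analyses of covariance may stay as secondary analyses. State that the RMDQ is completed at baseline, and reword the sample size remark so that the gain from between-visit correlation is tied to this adjustment.

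The cost is a few sentences of text, with no new data collection (provided the RMDQ is the baseline disability measure) and no additional participants.

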**Methods/Design:**

A randomized controlled trial comparing a combined intervention, consisting of internet-based CBT utilising MoodGYM plus multimodal manual therapy, to multimodal manual therapy alone for patients with chronic LBP. Multimodal manual therapy will be delivered by experienced chiropractors and physiotherapists. Treatment sessions will consist of a combination of joint and soft tissue mobilisation; spinal manipulation as well as muscle and fascia massage; education and reassurance; and rehabilitative exercise prescription. In total, 108 adult participants will be recruited from multiple chiropractic and physiotherapy private practices in Australia. Participants older than 18 years of age and diagnosed with chronic non-specific LBP will be included in the trial, where chronic LBP is defined as continuous or fluctuating pain for a minimum of three months.

The Keele STarT Back screening tool will be used to screen for potential participants who are in the medium risk category. The primary outcomes are self efficacy and disability measured by the Patient Self-Efficacy Questionnaire (PSEQ) and Roland Morris Disability Questionnaire (RMDQ) respectively. Secondary outcome measures will assess pain, catastrophising, depression, anxiety, stress and work ability. Participants will be randomly allocated into one of two groups. Both groups will receive an upper limit of 12 multimodal manual therapy sessions over a period of 8 weeks. The intervention group will also receive five weeks of MoodGYM covering five modules in total. Assessment will be conducted at pre-treatment, post-treatment 8- and follow-up at 26- and 52 weeks. In addition, a verbal pain measure will be completed by the treating practitioner at time of treatments on an 11-point VAS. The primary data analysis will be by intention to treat using a linear mixed model for each outcome.

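### Two primary outcomes at three visits are tested with unadjusted LSD contrasts and no success rule, and the stated 80% power is that of one such contrast

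*Protocol article*

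**What the plan says.** Under Primary outcomes, the between-group differences in PSEQ and RMDQ are primary "at the conclusion of treatment (8 weeks), 6- and 12-month follow up". Two outcomes at three visits make six contrasts, and none is ranked above another.

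Under Statistical methods, the linear mixed models are meant "to test for between group differences in post-treatment PSEQ and RMDQ". Two sentences later, an interaction of group with time is added so as to permit "least significant difference (LSD) contrasts to be obtained between groups at each time point".

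Under Sample size calculations, one calculation is given. It starts from an "estimated moderate post-treatment between-group effect size (Glass’s delta) of 0.60 SD" and concludes that "a sample size of 46 per group would be required to show statistical significance" ("power of 80 %, alpha = 0.05"). The test is again named as LSD and equated with an independent-samples t-test. No outcome is named for the 0.60 SD effect.

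**The concern.** LSD is not silence on multiplicity. It is the choice to make each comparison at the full alpha, and it appears in both the analysis and the sample size text. With six co-listed primary contrasts and no statement of what counts as a positive trial, a report could present whichever contrast is significant as the primary finding. The type I error of that claim would be well above 5%.

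The family itself is also unclear. The Abstract uses post-treatment for week 8 and follow-up for weeks 26 and 52. On that usage, the first sentence of Statistical methods describes two tests, while the Primary outcomes section and the LSD sentence describe six.

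The power statement covers one contrast. The aim at the end of the Background is worded jointly (higher self-efficacy and less long-term disability), and the 80% is not the power for that.

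**Working it through.** **Inputs from the protocol article.** Two outcomes, three visits, alpha 0.05 per test, power 80%, effect 0.60 SD, 46 evaluable per group, 1:1 allocation, 15% dropout, 108 in total. Sidedness is not stated. Two-sided is assumed because a one-sided calculation gives 35 per group, far from 46.

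**Assumed.** The correlations among the six test statistics are not given. Ranges used: 0 to 0.9 between visits and 0 to 0.7 between outcomes, with the cross-visit, cross-outcome correlation taken as the product.

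**Step 1: the plan's own figure.**
- Normal approximation: n = 2(1.96 + 0.84)²/0.60² = 43.6, so 44 per group. The exact t-test gives 45.
- At 46 per group the exact power is 81.2%.
- Dropout: 92/0.85 = 108.2, and 108 × 0.85 = 91.8.
- The stated 46 and 108 therefore reproduce to within rounding. The 81% applies to each contrast at which a 0.60 SD effect holds.

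**Step 2: family-wise error, if any one of six significant results counts as success.** Under independence it is 1 − 0.95⁶ = 0.265. With correlated z-statistics (simulation under the global null):

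| Between visits | Between outcomes | P(at least one of six) |
|---|---|---|
| 0 | 0 | 26.5% |
| 0.5 | 0.5 | 22.0% |
| 0.6 | 0.5 | 20.7% |
| 0.7 | 0.5 | 19.2% |
| 0.8 | 0.7 | 15.9% |
| 0.9 | 0.7 | 13.7% |

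These are two-sided errors. Counting only results that favour the intervention, 22.0% becomes 11.1% and 13.7% becomes 6.8%, against a nominal 2.5%.

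**Step 3: the narrow reading, two outcomes at 8 weeks only.** Under independence it is 1 − 0.95² = 9.75%. At an outcome correlation of 0.7 it is 8.3%.

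**Step 4: power at 46 per group, 0.60 SD.** The noncentrality is 0.60 × √(46/2) = 2.88.
- One contrast, exact t-test: 81% at alpha 0.05; 72% at 0.025 (Bonferroni over two); 57% at 0.0083 (Bonferroni over six).
- Both outcomes at one visit, each at 0.05 (normal approximation): 0.8206² = 67% at correlation 0, rising to 74% at 0.7.
- Holm across the two outcomes at one visit, 0.60 SD on both (normal approximation): per outcome 80% at correlation 0 and 78% at 0.7; at least one outcome 93% and 84%.

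**Step 5: possible gain from baseline adjustment.** The standardised effect becomes 0.60/√(1 − r²), where r is the assumed correlation between baseline and outcome. At alpha 0.025 and 46 per group, power is 77% for r = 0.3 and 85% for r = 0.5. Both figures are before any loss from site clustering.

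**The case against.** The case on the other side has several parts.

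- **This is a condensed article, and an SAP may exist.** Hierarchies and alpha splits are often set there, so their absence alone would be no finding. That does not dispose of the point, because the article positively fixes LSD in two sections. A later plan that added an adjustment would depart from this text and from its stated power basis.
- **No any-one-of-six rule is stated.** This stands. A reader might infer that the trial simply has a 26% false-positive rate. The documents do not support that. The figure needs both this success rule and independence, and independence is implausible: the sample size section invokes correlation between visits, and the Discussion says self-efficacy correlates with improvement in disability. If success required significance on both outcomes at the same visit, the error under the global null would be about 0.8-3.6%. That is not a full defence: if one outcome truly responds, the three visits still inflate the error on the other.
- **Power.** A reader might infer that the 80% holds for only one of the six tests. It does not follow: each contrast has about 81% wherever 0.60 SD applies. What stands is that the figure is for a single unadjusted contrast, and that the effect is given only as a post-treatment one.
- **An omnibus gate could lie behind the term LSD.** Gating each outcome with a three-degree-of-freedom test would bring the error to about 5-9%. No such gate is written; the interaction is included only so that the contrasts can be obtained.

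**Conclusion.** The point holds in this form. The plan lists six primary contrasts, tests them without adjustment, states no rule for a positive trial, and describes its primary analysis in two ways that do not match. If any one significant contrast may be claimed, the family-wise error is about 14-22% for plausible assumed correlations, with 26.5% as the independence bound. On the 8-week-only reading it is 8-10%, still above 5% at every correlation examined.

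The sample size arithmetic is sound for what it computes. It does not give the power to show benefit on both outcomes (about 67-74% at one visit) or the power under multiplicity control. These figures rest on two-sided testing, 46 evaluable per group, a 0.60 SD effect on both outcomes where both are considered, and outcome correlations of 0 to 0.7 that the document does not supply.

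**What to change.** 1. Reconcile the Primary outcomes and Statistical methods sections by naming one primary time point, chosen to match the stated aim.
2. At that visit, test PSEQ and RMDQ with Holm at overall two-sided 0.05. Alternatively, state a co-primary rule that requires both at 0.05.
3. Make the other visits secondary: either tested in fixed order after success at the primary visit, or reported as estimates with confidence intervals.
4. Restate the power for the chosen rule at 46 per group. With Holm it is about 78-80% per outcome and 84-93% for at least one, with 72% as the worst case at alpha 0.025. For the co-primary rule it is about 67-74%. Any credit for baseline adjustment (77-85% at alpha 0.025 for an assumed baseline correlation of 0.3-0.5) should be set against the loss from site clustering.

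The cost is wording and a slightly less favourable stated power. No extra patients are needed if the figure is restated. If the sponsor instead wants 80% at alpha 0.025 without baseline adjustment, about 55 per group are needed: 55/0.85 = 64.7, so 65 per group and about 130 in total after 15% dropout. The rule should be fixed before unblinding, since choosing it afterwards would not be credible.

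### The secondary ANCOVA is given the task of testing for regression to the mean, which a baseline coefficient cannot do

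*Protocol article*

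**What the plan says.** In the protocol article, Statistical methods, the primary analysis is a mixed model: "The primary data analyses will be conducted using linear mixed models to test for between group differences in post-treatment PSEQ and RMDQ". The next paragraph turns to secondary analyses. There, "analysis of covariance will be used to test whether regression to the mean has occurred", and the article explains what it means by this: "that is whether the patient’s response is related to baseline values". The same paragraph gives the ANCOVA a second use: "separate analyses will be conducted to determine the effects of treatment at −8, −26 and −52 weeks". The minus signs are evidently typographical, since the follow-up visits elsewhere in the article are at 8, 26 and 52 weeks.

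The article does not say whether response means the follow-up score or the change from baseline. It states no conclusion to be drawn from the test and makes no further use of the result.

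**The concern.** The paragraph treats two different things as one. Regression to the mean is movement of extreme scores towards the average because the baseline was partly transient or measured with error. A relation between response and baseline is only an association, and it has several possible causes. Almost any repeated scale shows one.

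A significant baseline term would then be likely to appear in the results under the label of regression to the mean. Recruitment of consecutive new patients within a screening-score band (Participants) makes that explanation look plausible, so a reader could use it to discount a treatment effect, although the test gives no ground for doing so. If the real interest is in who benefits more, a baseline main effect does not answer that either.

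**Working it through.** **Inputs.** Sample size calculations gives an effect of 0.60 SD (Glass's delta), 80% power and an alpha of 0.05, and says that on these terms "a sample size of 46 per group would be required to show statistical significance". It adds 15% for dropout and reaches 108 in total. Completers: 2 × 46 = 92. The baseline-to-follow-up correlation r is not given, so 0.3 to 0.9 is an assumed range.

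**The plan's own figure.** For 0.60 SD, two-sided 0.05 and 80% power, the normal approximation gives 44 per arm and the t-test 44.6, so 45. At 46 per arm the t-test has 81.2% power. 92 / 0.85 = 108.2. The stated 46 and 108 therefore reproduce, and the sample size is not at issue here.

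**How often the baseline term is significant.** The model is outcome = group + baseline, with standardised scores, equal variances at both visits and no treatment effect. The approximate size of the test statistic is:

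- follow-up score as response: r√n / √(1 − r²)
- change as response: (1 − r)√n / √(1 − r²) = √n · √((1 − r)/(1 + r))

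With √92 = 9.59 this gives, for example, 0.3 × 9.59 / 0.954 = 3.02 for follow-up score at r = 0.3. For change it gives 9.59 × √(0.1/1.9) = 2.20 at r = 0.9. The two-sided threshold is about 1.96. Simulation (4,000 trials per row, n = 92) gives these rejection rates:

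| r | follow-up score | change |
|---|---|---|
| 0.3 | 83% | 100% |
| 0.4 | 98% | 100% |
| 0.5 | 99.9% | 100% |
| 0.6 | 100% | 99% |
| 0.7 | 100% | 97% |
| 0.8 | 100% | 87% |
| 0.9 | 100% | 58% |

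Repeat runs differ by about one percentage point.

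**Does the test discriminate?** The table alone does not settle this, so four constructed situations were simulated at the same n.

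| Situation | Mean slope, change on baseline | Rejection, change | Rejection, follow-up score |
|---|---|---|---|
| A. Measurement error only (reliability 0.6), no true change | −0.40 | 99.5% | 100% |
| B. Error-free baseline, real response depending on baseline | −0.40 | 99.5% | 100% |
| C. No regression to the mean (follow-up slope 1) | 0.00 | 5% | 100% |
| D. Measurement error as in A, offset by true divergence | 0.00 | 5% | 100% |

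A and B have different causes and give the same slope and the same rejection rate. In C there is nothing to find, yet the follow-up-score version always rejects. In D measurement-error regression is present, and the change version rejects only at the nominal 5%. The change version is right in C, but it cannot tell A from B or C from D.

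**The treatment contrast.** In the same simulations the ANCOVA group term kept its type I error, at 4.7% to 5.3% across r. Its power for 0.60 SD was 86% at r = 0.3 and 91% at r = 0.5.

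**The case against.** The best defence has four parts.

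1. *High rejection is not error.* With equal variances and r below 1, scores do regress in the descriptive sense in every simulated trial. Frequent rejection for change is then power, not false alarm. This stands, and it is why the point rests on situations A to D and not on the rejection table alone. The near-certainty also weakens for change when r is high (58% at 0.9).

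2. *The model is not spelled out.* A condensed article may leave the terms to an analysis plan that is not shown, and nothing excludes an interaction. That is fair as to detail. But the article does fix the purpose and its definition, and the definition concerns response and baseline without reference to group. More detail on model terms would not make that definition a test of regression to the mean.

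3. *Nothing depends on it.* The analysis is secondary, no decision rule uses it, and the ANCOVA has a legitimate second use in estimating treatment effects. This stands and limits the weight of the point.

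4. *Per-visit ANCOVAs are ordinary.* A reader might object that they use only participants seen at each visit. The primary mixed model already uses incomplete visits, so running them alongside it is a matter of preference.

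Two stronger readings are tempting. One is that the trial would reach a wrong conclusion. The article states no conclusion, and regression to the mean may well occur in patients enrolled when they seek care, so a claim that it occurred could be true. The other is that the treatment result is biased. The documents do not support that: regression to the mean acts on both randomised arms alike in expectation, and the adjusted contrast kept its error rate.

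**Conclusion.** The point holds as a misassigned purpose for a secondary analysis. The baseline coefficient cannot establish regression to the mean under either meaning of response. With the follow-up score it is significant in 83% to 100% of trials over r = 0.3 to 0.9, including when no regression to the mean exists. With change it is significant in 97% or more up to r = 0.7, falling to about 87% and 58% at 0.8 and 0.9, and it does not identify the cause. Any report on this basis that regression to the mean had occurred would be unsupported.

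These rates assume 92 completers, the stated range of r, normal scores, equal variances and a test of the baseline main effect. The failure to separate A from B does not depend on the value of r. The primary estimates, their error rate, the sample size and the ANCOVA treatment contrast are untouched.

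**What to change.** - Delete the regression-to-the-mean purpose and its definition from Statistical methods.
- Describe the secondary analysis as a baseline-adjusted estimate of the treatment effect at 8, 26 and 52 weeks. Preferably obtain it by including the baseline score as a covariate in the mixed model.
- If dependence of benefit on baseline is of interest, add one exploratory group-by-baseline interaction for PSEQ and one for RMDQ, each reported as an estimate with a confidence interval.

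The cost is one reworded paragraph. The baseline scores are already collected, so no new data are needed. The interaction will be imprecise: with a standardised baseline and 46 per arm, the 95% half-width is about 1.96 × 2 × √(1 − r²) / √92. At r = 0.5 that is 1.96 × 2 × 0.866 / 9.59 = 0.35 SD of outcome per SD of baseline. It should be presented as exploratory for that reason.
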